### Recruitment and randomization

Cancer patients will be identified through the Netherlands Cancer Registry and recruited via treating physicians of several (university) hospitals in the Netherlands. Potentially eligible patients will receive a personalized letter from their treating physician, informing them about the study and the cognitive rehabilitation program. Patients will be asked to respond via post (response card), email, or phone whether or not they are interested in participation. In case a patient does not respond, a reminding letter will be sent after 3 weeks. Patients who express interest in participation will receive a phone call from the study team for further screening (e.g., a check of their employment status) and to provide additional information about the trial. Patients will be invited by e-mail to complete the baseline measurement (i.e., an online questionnaire and an online neuropsychological assessment) in case they fulfill all criteria, are motivated, and are willing to comply to the trial procedures. After completion of this baseline measurement, a session (face-to-face or using videoconference) with a therapist (e.g., neuropsychologist, occupational therapist) will be planned to discuss outcomes of the neuropsychological assessment, followed by collaborative treatment goal setting.

Upon receipt of all baseline information and after the session with the therapist, patients will be randomly allocated to the basic intervention arm (*N* = 87), the extensive intervention arm (*N* = 87), or the waitlist control group (*N* = 87), using randomized design in the computerized program ALEA. Minimization will be applied for the presence of cognitive impairment on the neuropsychological assessment to equalize group sizes. Blinding of participants and professionals is not possible for this type of intervention. Further, blinding for assessment is not applicable since measurements will be computer-based. A flow diagram of the recruitment procedure is outlined in Fig. 1. Figure 2 shows a schedule of enrolment, interventions, and assessments.

**Fig. 1 Fig1:**
[figure not shown]
Overview of the study design

**Fig. 2 Fig2:**
[figure not shown]
Schedule of enrolment, interventions, and assessments

### Intervention

The cognitive rehabilitation program will be based on the protocol of a frequently used meta-cognitive strategy approach applied in many rehabilitation centers in the Netherlands (i.e., “Niet Rennen Maar Plannen”). In cooperation with the creators of this protocol, we will adapt it for work-related cognitive problems and for online use. Patients and professionals will evaluate the adapted version of the protocol in several stages throughout its development. Both individual sessions and focus group interviews will be organized to obtain feedback, which will be used to evaluate and improve both content and user-friendliness of the adapted version of the intervention. The program will consist of several modules that can be used in a flexible way, depending on the specific individual problems and goals. As part of this study, therapists have undergone additional training in issues related to cancer-related cognitive impairment and problems occupationally active cancer survivors might experience at work. In both intervention arms, participants will receive access to a secured personal webpage, where all content relevant to the treatment sessions can be obtained. The basic and extensive intervention arms differ with regard to (1) therapy guidance (i.e., absent in the basic arm and present throughout the whole program in the extensive arm) and (2) intervention content. Table 1 shows an outline of the intervention content of the basic and the extensive cognitive rehabilitation program. The number and duration of sessions of both intervention arms may vary according to the individual needs and preferences of the participants, in line with the original face-to-face program on which the interventions are build. Therefore, there is no fixed number or duration of sessions in both intervention arms.

**Table 1 Tab1:** Outline intervention content

Modules	Content	Basic cognitive rehabilitation	Extensive cognitive rehabilitation
1. Psychoeducation	▪ Review current knowledge about cancer related cognitive impairment ▪ Learning how to identify “at risk” situations (at work) where cognitive failures arise	X X	X X
2. Fatigue-management	▪ Coping with fatigue (at work)	X	X
3. Cognitive behavioral therapy	▪ Coping with behavioral and emotional consequences of cognitive impairment (at work)	X	X
4. Communication	▪ Learning how to disclose your cognitive problems to colleagues	X	X
5. Strategy training: memory	▪ Learn and practice memory strategies at the workplace		X
6. Strategy training: information processing	▪ Learn and practice information processing strategies at the workplace		X
7. Strategy training: executive function	▪ Learn and practice planning and problem solving, flexibility and self- control strategies at the workplace		X
Therapy guidance			X

#### Basic cognitive rehabilitation program

The basic arm will consist of a brief cognitive training program without individual guidance throughout the intervention, which has to be completed in a period of 12 weeks.

#### Extensive cognitive rehabilitation program

The extensive arm will consist of a comprehensive training program, which has to be completed in a period of 12 weeks. The extensive cognitive rehabilitation program involves tailored therapy guidance in which the patients’ in-session reflection and homework assignments will be discussed. Cognitive strategy modules will be assigned by the therapist depending on the participants’ cognitive profile and personal treatment goals.

#### Waiting list control group

Participants in the waiting list control group will be offered the opportunity to follow the basic cognitive rehabilitation program after completion of the 26-week follow-up measurement.

### Data collection

Participants will be followed for 6 months in total and will be invited to complete measurements at three time points (at baseline (T0), treatment endpoint at 12 weeks post-randomization (T1) and at 26 weeks post-baseline (T2)). Measurements will be performed via a secured website, for which a link will be sent by email. Intervention effectiveness will be measured in terms of work-related goal attainment and secondary outcome measures. Secondary analyses will be performed to explore moderating and mediating processes. An overview of measures and mediating and moderating processes in treatment is presented in Fig. 3. Detailed descriptions of these secondary study measures are provided in Table 2.

**Fig. 3 Fig3:**
[figure not shown]
Dependent and independent measures, mediating and moderating processes

**Table 2 Tab2:** Study measures and corresponding instrument

Variable	Instrument	Details
*Primary outcome*		
Goal Attainment Scaling	GAS	▪ 3 personalized treatment goals
		▪ 6-point scale
*Secondary outcomes*		
Cognitive problems	CSC-W DV	▪ 19 items, 5-point scale
		▪ Score range: 0 (never) to 4 (always)
		▪ Cronbach’s alpha: 0.95
Work ability	WAI	▪ 1 item, 10-point Likert scale
Work functioning	WRFQ	▪ 27 items
		▪ Range 0 to 100; higher scores indicate better work functioning.
		▪ Subscales: work scheduling demands, mental demands, social demands, physical demands, and output demands
		▪ Cronbach’s alpha: 0.91–0.96
Absenteeism and presenteeism	iPCQ	▪ 6 items
		▪ Subscales: absenteeism, presenteeism
Need for recovery	VBBA	▪ 11 items (subscale)
Health-Related Quality of Life	SF-36	▪ 36 items, dichotomous and 3- to 6-point Likert scales
		▪ Subscales: vitality, physical functioning, bodily pain, general health perceptions, physical role functioning, mental health, emotional role functioning, and social role functioning
		▪ Score range: 0–100; higher score indicates higher levels of functioning/ well-being.
		▪ Time frame: past week
		▪ Cronbach’s alpha: 0.66–0.91 (mean 0.84)
Fatigue	SF-36	▪ 4 items (subscale)
Coping	CERQ	▪ 36 items, 5-point Likert scale
		▪ Score range: 0 (never) to 5 (always)
		▪ Subscales: self-blame, acceptance, rumination, positive refocusing, refocus of planning, positive reappraisal, putting in to perspective, catastrophizing and other blame
Neuropsychological function	ACS	▪ 7 different neuropsychological tasks
		▪ Online assessment
		▪ Cognitive domains: executive functioning, information processing speed, attention, working memory, verbal learning and memory, psychomotor speed.
		▪ The ASC is usable a reliable for the oncology setting, with test–retest correlations in the range 0.29 up to 0.78, which is comparable with traditional tests.
		▪ Concurrent validity with traditional tests is medium to large.
Work involvement	WIS	▪ 6 items, 5-point scale
		▪ Score range: 1 (totally disagree) to 5 (totally agree). High scores indicate a high work involvement
Job characteristics	JCQ	▪ 35 items, ordinal 4-point scales
		▪ Score range: 1 (totally disagree) to 4 (totally agree).
Depression and anxiety	HADS	▪ 14 items, 4-point Likert scale
		▪ Subscales: depression, anxiety
		▪ Score range: 0–42
		▪ Time frame: past week
		▪ Cronbach’s alpha: 0.68–0.93
		▪ Cut off: a score of 11 and over indicates the possible presence of clinical depression.

### Study measures

#### Sociodemographic and clinical data

Sociodemographic data including age, gender, marital status, number of children living at home, education, breadwinner status (sole/shared) will be obtained via questionnaire. Clinical information including cancer site, month/year of diagnosis, received (and future) treatment(s), (i.e., surgery, radiation, chemotherapy, immunotherapy, targeted treatment, hormonal therapy other medication), recurrence(s) of the disease, and comorbidity will be obtained from the medical records, Netherlands Cancer Registry, and via self-report. Information on general employment issues and on work accommodation, including employment sector, type of employment (fixed/temporary), years of work experience, and working hours and days per week according to employment contract, will be acquired via questionnaire.

#### Primary outcome measure

The primary outcome for this study will be individually defined work-related treatment goals, using the 6-point Goal Attainment Scale (GAS) on personal outcome (− 3, achievement of the goal after training is worse; − 2, achievement of the goal is the same; 1, partial achievement of the goal; 0, achievement of the goal; 1, exceeding the goal; and 2, greatly exceeding the goal) [33]. Patients will formulate three treatment goals and define the six outcome levels at baseline, in collaboration with their therapist. Attainment of the goals is measured in a standardized way, i.e., an overall GAS *T*-score will be computed for each participant on the basis of aggregated GAS scores involving attainment of multiple personal treatment goals, according to a summary scoring algorithm that calculates the extent to which patients’ goals are met.
$$ T=50+\frac{10\sum {w}_i{x}_i}{{\sqrt{\left(1\hbox{-} \rho \right)\kern0.5em \sum {w_i}^2+\rho \left(\sum {w}_i\right)}}^2} $$

*T* is the composite score, *w*_*i*_ is the weight assigned to goal_*i*_ (based on the patients prioritization), *x*_*i*_ is the original score for goal_*i*_ ranging from − 3 to + 2, and *ρ* is the estimated correlation between goal scores. The *T*-score has a mean of 50 and a standard deviation of 10. *w*_*i*_ is considered as equally relevant for each goal and thus assigned 1. Based on previous studies, correlation between the goal scores is constant and can be set at 0.3 [33]. Goals will be set at baseline (T0), and evaluated by patients (of all study arms) in collaboration with the cognitive therapist at T1 and T2. Due to practical reasons, this scoring of the level of attainment will be done by telephone. An independent assessor will perform quality checks on the use and scoring of GAS during the initial phase of the trial, to assure fidelity of the GAS-protocol.

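### The printed scoring of the primary outcome has two errors: code 1 labels two goal levels and −1 is missing, and the T-score formula squares the wrong term

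*Protocol article*

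**What the plan says.** All of this stands in the Protocol article, section Primary outcome measure.

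- **Levels.** Worse is coded −3 and unchanged −2, both with a printed minus sign. Then come "1, partial achievement of the goal; 0, achievement of the goal; 1, exceeding the goal", and finally 2 for greatly exceeding the goal. The printed codes are therefore −3, −2, 1, 0, 1, 2. Patient and therapist "define the six outcome levels at baseline", and the goal score entering the formula is described as "ranging from − 3 to + 2".
- **Goals and weights.** "Patients will formulate three treatment goals", and the weight "is considered as equally relevant for each goal and thus assigned 1".
- **Formula.** T is 50 plus ten times the weighted sum of goal scores, divided by a root. The exponent 2 stands on the whole root, and the sum of weights inside it carries no square.
- **Correlation and scale.** The "correlation between the goal scores is constant and can be set at 0.3", and the T-"score has a mean of 50 and a standard deviation of 10".

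Nothing elsewhere in the article corrects either item. Table 2 gives only the number of goals and of scale points. The Statistical analysis section relies on scoring algorithms from the literature and points back to the Methods.

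**The concern.** Six levels over the stated range need six different codes, and the list supplies five. The duplicated code belongs to two levels on opposite sides of full achievement, so the list as printed is not an ordered scale. A patient who moves from partly reaching a goal to fully reaching it would lose points.

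The formula disagrees with the text around it. The text fixes a value for the correlation and states an SD for T, but with the weights it prescribes, the printed expression does not depend on the correlation and does not deliver that SD.

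What is at stake is the written definition of the primary endpoint. Someone building the scoring program or the GAS form from this section would have to notice both errors and repair them.

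**Working it through.** **Inputs**, all from Primary outcome measure: three goals, every w = 1, ρ = 0.3, x from −3 to +2, stated SD of T = 10.

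**Codes.** The integers from −3 to +2 are −3, −2, −1, 0, 1, 2, which is six values. The printed list is −3, −2, 1, 0, 1, 2: five distinct values, with 1 used twice and −1 missing. The levels are listed from worst to best, so only −1 fits between −2 and 0.

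**Denominator as printed.** With w = 1 and three goals, Σw² = 3 and Σw = 3.

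[√((1−ρ)Σw² + ρΣw)]² = (1−ρ)×3 + ρ×3 = 3 for every ρ. At ρ = 0.3 this is 2.1 + 0.9 = 3.0.

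So T = 50 + (10/3)Σx = 50 + 3.33 Σx, and ρ has dropped out.

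**Denominator with the square on the sum of weights, inside the root.**

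√((1−ρ)Σw² + ρ(Σw)²) = √(0.7×3 + 0.3×9) = √4.8 = 2.191.

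So T = 50 + 4.56 Σx.

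**Attempt to reproduce the stated SD of 10.** Assumption: each goal score has mean 0 and SD 1, and any two correlate at 0.3, the scaling under which a T-score has SD 10. Then Var(Σx) = 3 + 6×0.3 = 4.8, so SD(Σx) = 2.191.

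| Denominator | Value | SD of T = 10 × 2.191 / denominator |
|---|---|---|
| As printed | 3.000 | 7.30 |
| Root with no square anywhere | √3 = 1.732 | 12.65 |
| Square on the sum of weights | 2.191 | 10.00 |

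Of these three readings, only the last gives the stated SD.

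**Effect on scores** (same level on all three goals, ρ = 0.3):

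| Goal score | T, printed formula | T, corrected formula |
|---|---|---|
| −3 | 20.0 | 8.9 |
| −2 | 30.0 | 22.6 |
| −1 | 40.0 | 36.3 |
| 0 | 50.0 | 50.0 |
| +1 | 60.0 | 63.7 |
| +2 | 70.0 | 77.4 |

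Three partly achieved goals score 36.3 with code −1 and 63.7 with the printed code 1, a gap of 27.4 points under the corrected formula. Under the printed formula the gap is 60.0 − 40.0 = 20.0 points. With either formula, the printed code puts partial achievement level with exceeding the goal and above full achievement.

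**Effect of the formula error alone.** The ratio of denominators is 2.191/3 = 0.730. Each patient's distance from 50 is multiplied by the same 0.730. A linear rescaling multiplies estimates and standard errors alike, so test statistics, p-values and standardised effect sizes stay the same. Raw T-scores and raw T differences shrink by 27%.

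**The case against.** The strongest reply is that these are printing slips which the section itself resolves. The order of the levels, their number and the stated range leave only −1 for partial achievement, and the stated SD of 10 points to the correct denominator. The analysis section relies on published scoring rules, therapists are trained in GAS, and an independent assessor checks scoring early in the trial. A sign lost in typesetting or text conversion cannot be fully excluded, although the minus signs on −3 and −2 survive in the same sentence. Nearly all of this stands: the intended versions can be inferred, and nothing here shows that data will be mis-scored. It does not make the printed definition correct.

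It is also fair that the formula error changes no inference. The sample size rests on a standardised effect (f = 0.2, d = 0.4), and the Discussion interprets GAS through effect sizes.

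A reader might infer four further things that the article does not support:

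- *That a mean of 50 is wrong because an unchanged patient scores 22.6.* Mean 50 and SD 10 are the nominal T-score convention. One patient's value does not refute a mean, and the SD check above uses the same convention.
- *That patients with fewer than three goals become non-comparable.* The article specifies three goals and makes no provision for fewer.
- *That the text gives a reason why the correlation matters.* It only sets the value, as constant and based on previous studies.
- *That the cost-effectiveness ratio is distorted.* The Cost-effectiveness section expresses it per relevant achievement of work goals, not explicitly per T-point, so an effect of the rescaling cannot be determined.

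**Conclusion.** Both errors stand as a fault in the written definition of the primary endpoint.

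The duplicate code is the more serious. It contradicts the section's own six levels and range and, if followed, breaks the ordering: three partly achieved goals would score 63.7 instead of 36.3 (corrected formula), above full achievement at 50. That is the size of a literal application, not an expected error in the trial data.

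The misplaced square makes the stated correlation of 0.3 inert and gives an SD of 7.30 instead of 10, assuming goal scores with mean 0, SD 1 and common correlation 0.3. With three equally weighted goals its consequence is limited to raw T-scores and raw T differences, which are scaled by 0.73.

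A reader might conclude that the trial's results or power are compromised. The article does not support that: both slips look typographical, and the power calculation does not depend on the scale of T.

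**What to change.** 1. Print the six codes as −3, −2, −1, 0, +1, +2, with −1 for partial achievement.
2. Print the formula as T = 50 + 10 Σwx / √((1−ρ)Σw² + ρ(Σw)²), and state that with three goals, w = 1 and ρ = 0.3 the denominator is √4.8 = 2.19.
3. Check the scoring program and the GAS form against both. Two test cases are enough: −1 on all three goals must return 36.3, and +1 on all three must return 63.7.

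The cost is a text correction of two symbols and a short check of the program and form. Design, sample size and analysis model stay as they are.

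### The printed GAS scoring key gives partial achievement the code 1, which contradicts the protocol's own six-level scale from -3 to +2; the code should read -1

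*Protocol article*

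**What the plan says.** The protocol article defines the primary outcome under Primary outcome measure, "using the 6-point Goal Attainment Scale (GAS) on personal outcome". Six verbal levels follow in rising order: worse, same, partial, achieved, exceeded, greatly exceeded. The lowest is printed as -3. The next reads "2, achievement of the goal is the same", with a minus sign printed directly before the 2. The remaining four read "1, partial achievement of the goal; 0, achievement of the goal; 1, exceeding the goal; and 2, greatly exceeding the goal", with no minus sign before the first of them.

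The same section sends these codes into the T-score as the goal scores x_i, described as "ranging from − 3 to + 2". It also fixes the other inputs:

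- Number of goals: "Patients will formulate three treatment goals".
- Weights: each w_i "is considered as equally relevant for each goal and thus assigned 1".
- Correlation: the "correlation between the goal scores is constant and can be set at 0.3".

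Table 2 also lists GAS as a 6-point scale. No other place in the article prints a code for partial achievement.

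**The concern.** The printed codes are -3, -2, 1, 0, 1, 2. The value 1 appears twice and -1 does not appear. The verbal levels rise steadily, but the numbers go up from -2 to 1, down to 0 and up again to 1. Read literally, a patient who partly reaches a goal scores the same as one who exceeds it, and better than one who reaches it exactly.

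This is the only scoring key shown for the only primary outcome. The T-score built from it is the response in the growth curve model and in the moderation analysis by cognitive impairment (Statistical analysis). GAS is also the effect measure in the cost-effectiveness ratio (Cost-effectiveness). A scoring form or program that copied the printed key would carry a non-monotone endpoint into all of these.

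**Working it through.** **Step 1: number of levels.** The protocol states 6 points and a range of -3 to +2. The integers in that range number 2 - (-3) + 1 = 6, so label and range agree. The printed codes have five distinct values: -3, -2, 0, 1, 2. The stated six levels are not reproduced. The only unused integer is -1, and the only level out of order is partial achievement. Putting -1 there gives -3, -2, -1, 0, 1, 2: six distinct values in the order of the verbal levels.

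**Step 2: T-score inputs.** All come from Primary outcome measure: three goals, w_i = 1, rho = 0.3. With the square on the sum of weights, inside the root:

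T = 50 + 10 × Σ w_i x_i / √[(1 - rho) Σ w_i² + rho (Σ w_i)²]

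Denominator = √(0.7 × 3 + 0.3 × 9) = √4.8 = 2.191

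One level on one goal is worth 10 / 2.191 = 4.56 T points. Coding +1 in place of -1 is a shift of two levels, or 20 / 2.191 = 9.13 T points per partly achieved goal. That is about 0.9 of the stated standard deviation of 10.

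**Step 3: the formula as typeset in the text at hand.** There the exponent 2 stands outside the root, so the denominator becomes 0.7 × 3 + 0.3 × 3 = 3.0. The shift per goal is then 20 / 3.0 = 6.67. The misplaced exponent may itself be a typesetting artefact, so both versions are shown.

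**Step 4: patients with some goals partly achieved and the rest fully achieved.**

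| Partly achieved goals | T, code 1 as printed (denominator 2.191) | T, code -1 (denominator 2.191) | T, code 1 as printed (denominator 3.0) | T, code -1 (denominator 3.0) |
|---|---|---|---|---|
| 0 | 50.00 | 50.00 | 50.00 | 50.00 |
| 1 | 54.56 | 45.44 | 53.33 | 46.67 |
| 2 | 59.13 | 40.87 | 56.67 | 43.33 |
| 3 | 63.69 | 36.31 | 60.00 | 40.00 |

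Three exceeded goals give 50 + 30 / 2.191 = 63.69, which is the same value that the printed code gives to three partly achieved goals. The difference for three partly achieved goals is 63.69 - 36.31 = 27.39 points before rounding of the terms, or 60 - 40 = 20 with the formula as typeset. Under both denominators the printed code ranks partial above full achievement, and -1 restores the order.

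**The case against.** The strongest reply is that the section corrects itself. The label, the six ordered levels and the stated range leave -1 as the only possible code, so a careful reader is not misled about the intent. This stands. It makes the point a wrong printed value and not an undefined endpoint.

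A reader might go further and infer that therapists scored patients with +1 in the telephone assessments. The document does not support that. It says that the levels are defined with the patient at baseline and that attainment is later rated by telephone. It does not say that the printed list is the working score sheet or the program. It also provides for an independent assessor to check the use and scoring of GAS in the initial phase, and the Discussion adds GAS training for therapists. Such checks could catch a key that ties partial achievement with exceeding the goal, although the text does not say that they cover the numeric codes.

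A reader might also infer that partial achievement is the level at which a programme effect would mainly show. The article gives no expected distribution of GAS levels, so this cannot be claimed.

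Two further objections are fair in part. The size depends on how the T formula is read, which is why both readings are given; the inversion does not depend on it. And the text was read from a PDF by a program, so a lost character cannot be excluded. However, the minus signs on -3, on -2 and in the range all survived in the same section, so an error in the article is the likelier explanation. Comparison with the published page settles it.

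**Conclusion.** The point holds as an error in the printed definition of the primary outcome. Partial achievement carries the code 1 where the protocol's own description of the scale requires -1, probably through a dropped minus sign. It is not evidence that any patient was scored wrongly.

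The size is conditional on the key being programmed as printed, with three goals, unit weights and rho = 0.3. Each partly achieved goal would then be 9.1 T points too high, and three would give 63.7 instead of 36.3. With the formula as typeset, the error is 6.7 points per goal, and three give 60 instead of 40. The effect on a between-arm difference cannot be derived, because it depends on how often each arm ends at partial achievement, and the article does not give that.

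The correction should be made despite the probable cause, because the value enters the primary T-score directly and the remedy is trivial.

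**What to change.** Print -1 as the code for partial achievement in the protocol, so that the key reads -3, -2, -1, 0, 1, 2. Then confirm that the GAS manual used by therapists, the telephone scoring form and the analysis program use -1, and that no score already entered used +1 for partial achievement. While doing so, check that the program places the square on the sum of weights inside the root.

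The cost is a one-character correction and a short check of the form, the code and any data entered. The design, the sample size and the analysis model are unaffected.

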### Cost-effectiveness

Incremental cost will be calculated and, by using incremental QALYs and GAS scores, expressed as the incremental cost-utility ratio (ICUR) and incremental cost-effectiveness ratio (ICER), respectively. The ICUR and ICER will be measured for both intervention groups. ICUR represents the costs required for the particular intervention to generate one additional QALY in comparison with care as usual (control group). ICER represents incremental costs per relevant achievement of work-related treatment goals (GAS) over a time period of 6 months. Both ratios will be estimated by bootstrap analyses. As an indication of whether an intervention will be considered cost-effective, the ICUR is compared to a range of ceiling ratios varying from €20k per QALY to €80k per QALY in the Netherlands, with €30k per QALY commonly accepted as the prevailing ceiling ratio. In addition, cost-effectiveness acceptability curves will be used to inform decision-makers on the probability that the cognitive rehabilitation program is cost-effective.

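### The printed GAS T-score formula squares the whole root, so rho cancels; if programmed literally, every deviation from 50 is 27% smaller than the standardised form gives

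*Protocol article*

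**What the plan says.** All of the scoring rules are in the protocol article, Primary outcome measure:

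- Number of goals: "Patients will formulate three treatment goals and define the six outcome levels at baseline". Each goal is scored from −3 to +2.
- Weights: each w_i "is considered as equally relevant for each goal and thus assigned 1".
- Correlation: "correlation between the goal scores is constant and can be set at 0.3".
- Resulting scale: T "has a mean of 50 and a standard deviation of 10".
- Formula as printed: T = 50 + 10·Σ(w·x) / {√[(1−ρ)·Σw² + ρ·Σw]}². The root closes before the exponent, and Σw under the root carries no square.

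The Statistical analysis section says that GAS scores will follow published algorithms and refers the reader back to the methods, where this is the only formula. The later Cost-effectiveness section, on the analysis, forms its two ratios "by using incremental QALYs and GAS scores, expressed as the incremental cost-utility ratio (ICUR) and incremental cost-effectiveness ratio (ICER), respectively". It then describes the second one this way: "ICER represents incremental costs per relevant achievement of work-related treatment goals (GAS) over a time period of 6 months".

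**The concern.** A root that is squared at once undoes itself, so the printed denominator cannot do the standardising for which rho was introduced. The section fixes a value for rho and states an SD for T, and the printed formula is consistent with neither.

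The formula defines the primary outcome. A programmer who follows it literally produces T-scores on a different scale from the stated one. A programmer who uses the standardised form produces T-scores that cannot be reproduced from the article. At stake are the absolute T values, the raw differences between arms in T-points, comparison with the stated mean and SD, and any economic ratio expressed per T-point.

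**Working it through.** **Inputs**, all from Primary outcome measure: n = 3 goals, w = 1, ρ = 0.3, stated SD of T = 10. One assumption is added: single-goal scores have mean 0 and SD 1 with correlation ρ, which is the condition under which a T-score of this kind has mean 50 and SD 10. The check concerns the formula, not whether the trial's goal scores will meet that condition.

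**Step 1: the printed denominator.** {√[(1−ρ)·3 + ρ·3]}² = (1−ρ)·3 + ρ·3 = 3 for any ρ. Hence T = 50 + (10/3)·Σx, that is, 50 plus ten times the mean goal score.

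**Step 2: can the stated SD of 10 be reproduced?** Var(Σx) = 3 + 6 × 0.3 = 4.8, so SD(Σx) = √4.8 = 2.191. Then SD(T) = 10 × 2.191 / denominator. Four placements of root and square were tried:

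| Denominator | Value | SD of T |
|---|---|---|
| As printed: root, then squared | 3 | 7.30 |
| Square on Σw, inside the root | √(0.7×3 + 0.3×9) = √4.8 = 2.191 | 10.00 |
| Root, no square | √3 = 1.732 | 12.65 |
| Square on Σw, no root | 4.8 | 4.56 |

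Only the second placement gives the stated SD, and it is also the one in which ρ does its work.

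**Step 3: size of the difference.** The ratio of printed to corrected deviation from 50 is 2.191/3 = 0.730, so deviations are 27% smaller. One level on one goal is worth 10/3 = 3.33 T-points as printed and 10/2.191 = 4.56 as corrected.

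| All three goals at | Σx | T as printed | T corrected |
|---|---|---|---|
| −3 | −9 | 20.0 | 8.9 |
| −2 (unchanged) | −6 | 30.0 | 22.6 |
| 0 (achieved) | 0 | 50.0 | 50.0 |
| +1 | 3 | 60.0 | 63.7 |
| +2 | 6 | 70.0 | 77.4 |

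**Step 4: inference.** With three scored goals for everyone, one version of T is a linear function of the other. The arm difference and its SD are both multiplied by 0.730, so their ratio does not move. The effect size of d = 0.4 in the sample size section is therefore untouched, and so are the p-values and the power.

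**Step 5: economic ratio.** If the ICER denominator is a difference in T, it shrinks by the same factor and the cost per T-point is multiplied by 1/0.730 = 1.369, which is 37% more. If it is something else, such as a count of patients reaching a goal level, this factor does not apply.

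**Step 6: fewer than three scored goals.** The article does not describe this case. If it arose, the two versions would no longer differ by one constant. With two goals the denominators are 2 and √(0.7×2 + 0.3×4) = √2.6 = 1.612, so deviations are 19% smaller (1.612/2 = 0.806). With every goal at −1, two goals give 40.0 as printed and 37.6 as corrected; three goals give 40.0 and 36.3.

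**The case against.** The strongest reply is that this is a typesetting slip with no consequence. The exponent directly follows the bracket around the sum of weights, which is the last term under the root, so a small displacement turns the standardised form into the printed one. The same section reveals the intention through its SD of 10, its value for rho and its citation of a published scale, and the analysis section promises published algorithms. Nothing in the article shows that the scoring program uses the literal form. Much of this stands: a slip with correct code behind it is quite possible. But the notation is explicit as it is given, this is the only formula for the primary outcome, and the analysis section points back to it. The article alone cannot show which form is in use.

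A second reply is that the plan draws its conclusions from effect sizes, has no T-point threshold, and fixes three goals for everyone. This stands too. A reader might infer that the tests, the power or the sample size are wrong; they are not, because a linear rescaling leaves them as they were.

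A reader might also infer that the trial's cost-effectiveness ratio is overstated by 37%. The article does not support that. It mentions "by using incremental QALYs and GAS scores, expressed as the incremental cost-utility ratio (ICUR) and incremental cost-effectiveness ratio (ICER") but then words the result as a cost per relevant achievement of goals, without saying whether that is a T-point, a goal level or a responder. The 37% is conditional on the first of these.

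**Conclusion.** The printed formula is wrong by the article's own figures: it makes the stated rho irrelevant and gives an SD of 7.3 where 10 is stated, assuming goal scores with SD 1 and correlation 0.3. If it is programmed as printed, deviations from 50 and raw arm differences in T are 27% smaller than under the standardised form, given three goals, weight 1 and rho = 0.3. Hypothesis tests and standardised effects are not affected while every patient has three scored goals. The effect on the economic ratio is undetermined. Because the formula defines the primary outcome scale, it should be corrected, but the error does not threaten the trial's main inference.

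**What to change.** Correct the formula to T = 50 + 10·Σ(w·x) / √[(1−ρ)·Σw² + ρ·(Σw)²], and confirm that the scoring program uses this form. One test case is enough: three goals, all at −2, must give 22.6 and not 30.0. It would help readers to state the constant, 4.56 T-points per goal level for three equally weighted goals, but that is optional. If the ICER is to be expressed per T-point, say so in the Cost-effectiveness section, so that its scale is tied to the corrected formula. The cost is one moved exponent and one check of the program; no design element, sample size or test changes.
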